##### Reasoning and problem-solving

 The Stroop Colour and Word Test (SCWT) assesses processing speed, cognitive flexibility, and cognitive control [88]. Participants first read colour blocks and colour names aloud (two baseline tasks). They then name the ink colour of incongruent colour words (interference), requiring suppression of the habitual response to facilitate an unusual one. More time needed corresponds to lower performance. The Stroop interference effect is calculated as the increase in completion time from the baseline to the interference task, providing a general measure of executive functioning. The interference score is calculated by the equation: (colour-word reaction time) – ((colour reaction time + word reaction time)/2).

##### Subjective cognitive functioning

 The Cognitive Failure Questionnaire (CFQ) measures subjective cognitive functioning [89, 90] and includes 25 questions assessing attention and memory. Each question is scored between 0 (never) and 4 (very often), with higher total scores indicating more cognitive mistakes.

##### Observed cognitive functioning

 The Nurses’ Observation Scale of Cognitive Abilities (NOSCA) is a behavioural rating scale to examine cognitive abilities in service users, completed by participants’ case managers [91]. It consists of eight subscales, representing subdomains of cognition, using 39 items scored between 0 and 3, with higher total scores indicating better functioning.

##### Negative symptoms

 The Self Evaluation of Negative Symptoms (SNS) is a 20-item questionnaire assessing negative symptoms from the perspective of the service user [92] categorised in the five domains of negative symptoms – social withdrawal, diminished emotional range, avolition, anhedonia, and alogia. Items are scored on a Likert scale ranging from 0 (strongly disagree) to 2 (strongly agree), with higher scores indicating greater severity.

##### Self-efficacy

The Dutch version of the General Self-Efficacy Scale (GSES) comprises 10 items that evaluate self-efficacy, or the respondent’s general perception of their ability to achieve goals, overcome challenges, and perform well on tasks [93]. Participants rate items on a 4-point response scale from 1 (strongly disagree) to 4 (strongly agree). Responses are averaged to produce an overall score, and higher scores indicate greater self-efficacy.

##### Social functioning

The Social Functioning Scale (SFS) is a 79-item standard measure developed and validated for individuals with schizophrenia, demonstrating appropriate psychometric properties [94]. It includes subscales assessing social engagement or withdrawal, interpersonal functioning, current social activities, recreational activities, independence-competence, independence-performance, and employment. Both the observer-rated and self-rated versions are used, with higher scores indicating higher social functioning. Additionally, the Behapp smartphone application (www.behapp.com) objectively and passively measures social functioning in daily life, capturing sociability and social exploration [95]. After installation and activation with a unique code, Behapp runs in the background of participants’ smartphones, collecting data on communication events (e.g., incoming and outgoing calls), application usage (e.g., social or entertainment applications), and GPS-based location. Data are gathered in four 14-day phases aligned with T0-T3, and gathering is stopped automatically after completion of each phase. All information is encrypted, stored locally until secure upload, and the content of calls, messages, or applications is never recorded. Participants provide explicit consent for Behapp during inclusion, and opting out of Behapp does not affect study participation. Behapp has already proven feasible for use in individuals with schizophrenia [96].

#### In-depth interview

To examine service users’ metacognitive skills and subjective experiences, we use an adapted version of the Indiana Psychiatric Illness Interview (IPII), a semi-structured interview designed originally to elicit illness experiences and spontaneous metacognitive thoughts, which lasts 30–60 min [97]. For this study, the interview is revised to focus on cognitive experiences and everyday cognitive functioning. Responses are rated with the abbreviated Metacognitive Assessment Scale (MAS-A) as a rating scale [98, 99], adapted for this study to assess the metacognitive ability of cognitive functioning. The main adaptations in the IPII and MAS-A involved refocusing the content from mental illness to cognitive abilities, simplifying the language, and dividing complex items into shorter segments to improve accessibility. The MAS-A evaluates self-reflectivity, understanding the other’s mind, decentration, and mastery, and has consistently shown robust validity and reliability [98]. Higher scores on each subscale indicate a greater ability to form complex representations of oneself and others.

Additional open-ended questions explore subjective experiences with CIRCuiTS, its perceived impact on metacognition, daily functioning, supportive components, and potential areas for improvement.

A focus group with CIRCuiTS therapists further evaluates the in-depth interview. Based on established guidelines for focus group discussion research [100], this discussion may lead to further refinement of the interview scheme.

### Adverse event reporting

TDCS is regarded as a safe method with no evidence of short- or long-term harm when applied within established parameters [101]. Accordingly, the risk of adverse events is expected to be low. During each session, therapists will systematically document any participant-reported complaints and potential tDCS-related side effects (e.g., burning, headache, itching, tingling). All adverse events reported by participants, researchers, or health professionals will be assessed for seriousness and reported to the relevant parties in accordance with the Medical Ethics Review Committee of the University Medical Centre Groningen (METc) procedure.

### Participant timeline

An overview of enrollment, intervention, and assessments is shown in Table 1.

**Table 1 Tab1:** Schedule of enrolment, interventions, and assessments

Timepoint	Enrolment	Pre-intervention		Intervention	Post-intervention	6-months follow-up
	< T_0_	T_0_	T_1_		T_2_	T_3_
Enrolment						
Eligibility screen	x					
Informed consent	x					
tDCS safety checklist	x					
Randomisation						
Allocation			x			
Interventions						
CR + active tDCS				x		
CR + sham tDCS				x		
Assessments						
PANSS-6		x				
GAS		x (goals set)	x (outcome rated)		x (outcome rated)	x (outcome rated)
ILSS-I & -SR		x	x		x	x
COWAT		x	x		x	x
TMT-A & -B		x	x		x	x
BADS key search		x	x		x	x
WMS-IV visual reproduction		x	x		x	x
Digit Span (forward/backward)		x	x		x	x
WT-15		x	x		x	x
SCWT		x	x		x	x
CFQ		x	x		x	x
DEX-S & -I		x	x		x	x
NOSCA		x	x		x	x
SNS		x	x		x	x
GSES		x	x		x	x
SFS		x	x		x	x
Behapp		x	x		x	x
In-depth interview					x	

*BADS* Behavioural Assessment of the Dysexecutive Syndrome, *CFQ* Cognitive Failure Questionnaire, *COWAT* Controlled Oral Word Association Test, *CR* cognitive remediation, *DEX−S & −I* dysexecutive questionnaire – self & informant, *GAS* Goal Attainment Scale, *GSES* General Self−Efficacy Scale, *ILSS−I & −SR* independent living skills survey – informant & self−report, *NOSCA* nurses’ observational scale of cognitive abilities, *PANSS−6* The Positive and Negative Syndrome Scale – brief, *SCWT* Stroop Colour and Word Test, *SFS* Social Functioning Scale, *SNS* self−evaluation of negative symptoms, *tDCS* transcranial direct current stimulation, *TMT* Trail Making Test, *WMS−IV* Wechsler Memory Scale – Fourth edition, *WT−15* 15−word learning task

### Proposed sample size and power calculation

The sample size was determined for the primary objective, namely the within-subject effect of CR on daily functioning compared with the waitlist period in the non-concurrent multiple baseline design, pooled across tDCS conditions. The calculation was based on an anticipated effect size of d = 0.36 for daily functioning, derived from a prior study in the same target population using a compensation-focused CR approach [102]. Using a paired t-test for dependent groups (two-sided α = 0.05, power = 0.80, Cohen’s d = 0.36), a sample size of 50 participants per group is required. To account for an estimated dropout rate of 20%, we aim to recruit a total of 126 participants, equating to 63 individuals per group. Detailed descriptive outcome data from our pilot study are available in the Open Science Framework (https://osf.io/cj49e/) [65]. Pilot-derived effect-size estimates for everyday functioning were not used for formal powering because functional outcome assessment in the pilot was heterogeneous, and did not capture participant-reported benefits, suggesting insufficient sensitivity to detect CR-related change in this setting. Therefore, we based the effect size on prior evidence from the larger study mentioned above [102], which provides a more precise estimate.

The sample size for the in-depth interviews is determined by the participants’ willingness to participate and thematic saturation. Ideally, the sample size ranges from 10 to 20 participants, given the homogeneous nature of the sample and the narrow scope of the study topic. Data collection ceases once data saturation is achieved.

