## Method

### Trial design

This pragmatic, triple-blinded, randomised, sham-controlled multi-centre trial follows a non-concurrent multiple baseline design (Fig. 1). Recruitment and eligibility assessment are followed by enrolment into five cohorts, each comprising approximately 20–24 participants, spaced 16–20 weeks apart. After inclusion, participants complete two baseline assessments (T0, T1), separated by a 16-week waiting period serving as a within-subject control, offering greater internal validity than a between-subject design. This design enables all participants to receive the intervention and attain its potential benefits. After T1, participants are randomised to either CR + active tDCS or CR + sham tDCS. After the 16-20-week intervention period, outcomes are reassessed post-treatment (T2, within 2 weeks) and at 6-month follow-up (T3).

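### The stated 50 per group does not follow from the stated two-sided paired test, which needs 63 evaluable participants in total, and the target of 126 disagrees with both the pooled analysis and the planned cohorts

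*Protocol article*

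**What the plan says.** The section on proposed sample size and power calculation sizes the trial for "the within-subject effect of CR on daily functioning compared with the waitlist period in the non-concurrent multiple baseline design, pooled across tDCS conditions". It gives the test ("Using a paired t-test for dependent groups"), the error rates ("two-sided α = 0.05, power = 0.80") and "an anticipated effect size of d = 0.36 for daily functioning". From these it concludes that "a sample size of 50 participants per group is required". After an allowance for 20% dropout it continues: "we aim to recruit a total of 126 participants, equating to 63 individuals per group".

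Three other places bear on this:

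- Trial design plans "enrolment into five cohorts, each comprising approximately 20–24 participants".
- Randomisation and blinding describes only two groups, active and sham stimulation, allocated 1:1.
- Statistical analysis defines the primary effect as change during the intervention against change during the waitlist, pooling active and sham. It says that the trial is powered for this effect and not for the tDCS contrast, and it applies Holm across three primary outcomes.

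**The concern.** The required number, its unit and the recruitment total do not belong to one calculation.

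- **Number.** Test, sidedness, power and effect size are all stated, so the result can be checked, and 50 is not what they give.
- **Unit.** A paired test returns a number of people, each of whom contributes a pair. If the effect is "pooled across tDCS conditions", that number is a total, and the two stimulation arms give no reason to double it.
- **Total.** The doubled figure is larger than the planned cohorts add up to.

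Recruitment is ongoing, with 59 enrolled according to Trial status. The number at which it should stop is therefore a live decision, and its published justification cannot be reproduced.

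**Working it through.** **Inputs.** From the sample-size section: paired t-test, two-sided alpha 0.05, power 0.80, d = 0.36, dropout 20%. From Trial design: five cohorts of about 20 to 24. From Statistical analysis: Holm over three primary outcomes. Assumption: d is the mean difference divided by the SD of the differences. The article does not say this.

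**The plan's own chain.** 50 / (1 − 0.20) = 62.5, rounded up to 63; 2 × 63 = 126. This arithmetic is correct. The problem lies in the 50 and in the factor of 2.

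**Required n for the quoted test.** Power comes from the noncentral t distribution with n − 1 degrees of freedom and noncentrality d√n. At n = 50 the noncentrality is 0.36 × √50 = 2.546 and the two-sided critical value is 2.010.

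| Evaluable n | Two-sided power, 0.05 | One-sided power, 0.05 |
|---|---|---|
| 49 | 69.5% | 79.9% |
| 50 | 70.4% | 80.7% |
| 62 | 79.7% | 87.7% |
| 63 | 80.3% | 88.1% |

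The smallest n with 80% power is 63 two-sided and 50 one-sided. The normal approximation ((z for alpha + z for power)/d)² gives 60.6, so 61, two-sided, and 47.7, so 48, one-sided. It does not produce 50 either. A two-sample test at d = 0.36 needs 122 per arm two-sided or 96 one-sided, so a between-group calculation does not explain 50.

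**Another route to 50.** If d = 0.36 were standardised by the raw SD, the effect on the difference scale would be d/√(2(1 − ρ)), with ρ the correlation between the two measurements. Two-sided n is then 63 at ρ = 0.5, 51 at 0.6 and 39 at 0.7. It equals 50 near ρ = 0.61. The article states neither this scale nor a correlation.

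**Unit and dropout.** One pooled set of participants is analysed, so 63 is a total: 63 / 0.80 = 78.75, rounded up to 79 recruited. The article's 63 per group is 50 / 0.80, a recruited number. That it equals the 63 evaluable participants is a coincidence.

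**Cohorts.** 5 × 20 = 100 and 5 × 24 = 120. A total of 126 needs 126 / 5 = 25.2 per cohort.

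**Power that the planned numbers deliver** (d = 0.36, two-sided, 20% dropout):

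| Recruited | Completers | Power at 0.05 | Power at 0.05/3 (first Holm step) |
|---|---|---|---|
| 79 | 63 | 80.3% | 65.4% |
| 100 | 80 | 88.9% | 77.9% |
| 105 | 84 | 90.3% | 80.2% |
| 120 | 96 | 93.7% | 86.0% |
| 126 | about 100 (126 × 0.80 = 100.8) | 94.6% | 87.6% |

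At 0.05/3 the smallest n with 80% power is 84 completers, which is 84 / 0.80 = 105 recruited.

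**Sensitivity to the scale of d.** The analysed contrast is a difference of two changes, (T2 − T1) − (T1 − T0). If d were a raw-SD effect, and SDs and correlations were equal across visits (assumptions), the standardised effect would be d/√(6(1 − ρ)). The required n at two-sided 0.05 is then 184 at ρ = 0.5, 111 at 0.7 and 39 at 0.9.

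**The case against.** Four points can be made for the plan.

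1. **The trial has enough people.** The low n and the doubling work in opposite directions, and 100 to 126 recruited is well above 79. This stands. A reader might infer from a wrong sample size that the trial is underpowered; at d = 0.36 and alpha 0.05 the documents do not support that.
2. **The target is clear.** Within its own section the article gives one recruitment target, and the steps from 50 to 126 are correct arithmetic. This also stands. The fault is in the justification and in the disagreement with Trial design.
3. **The cohort sizes are approximate.** Reaching 126 takes 25.2 per cohort, about one more than the upper figure, and the shortfall at the top of the range is 6 people. So the cohorts do not rule out 126, and this part is a minor inconsistency. The two sections still imply different totals.
4. **The 50 may have another source.** A reader might conclude that a one-sided test was run. The match is exact, but the article says two-sided, and a raw-SD effect with a correlation near 0.61 gives 50 as well. The one-sided origin is an inference; that 50 does not follow from the stated inputs, with d on the difference scale, is not.

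A reader might also take 63 in total as what the trial needs, and as permission to recruit fewer. The article does not support that. Sixty-three is the output of the quoted t-test at 0.05, while the planned analysis applies Holm to three outcomes and compares two changes, with the scale of d unstated.

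**Conclusion.** The point holds as an error of justification. With d standardised by the SD of the differences, the stated test needs 63 evaluable participants in total (79 recruited at 20% dropout), and 50 gives 70.4% power instead of 80%. The per-group wording and the doubling contradict a pooled within-subject effect, and 126 lies above the 100 to 120 that the cohorts imply.

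Lack of power is not shown at d = 0.36 and alpha 0.05: 80 to 96 completers give 89% to 94%, and 100 give about 95%. At the first Holm step the margin is thinner, at about 78% with 80 completers and 86% with 96. These powers rest on the assumed scale of d and on 20% dropout.

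**What to change.** In the sample-size section:

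- State that the two-sided paired t-test at 0.05 with 80% power and d = 0.36 needs 63 evaluable participants in total, or 79 recruited at 20% dropout. Present this as the result of that test and not as the trial's full requirement.
- Delete the per-group wording from the calculation. If the split by arm is kept, give it only as a consequence of 1:1 allocation.
- State how d is standardised and whether it refers to a single change or to the difference between the intervention and waitlist changes. If it is on the raw scale, give the correlation assumed and redo the calculation.
- Reconcile this section with Trial design to one recruitment target, and do not use the correction to reduce it.
- State the two-sided power of that target at 0.05 and at 0.05/3, noting that 80% at the first Holm step needs 84 completers (105 recruited).

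The cost is corrected text in two sections. At d = 0.36 on the difference scale and alpha 0.05, no recruitment beyond the planned cohorts is called for.

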### Statistical analysis

Data analyses will follow an intention-to-treat approach using multilevel models implemented in R (‘lme4’ or ‘glmer’ packages). This approach accounts for the nested structure of repeated measures within participants and participants nested within centres. Model assumptions will be assessed using scatter plots of residuals and Quantile-Quantile (QQ) plots. Multilevel models are generally robust to moderate violations of normality. Models will be estimated using maximum likelihood, which uses all available data under a missing-at-random assumption.

We will build separate multilevel models for each primary and secondary outcome. Timepoint will be included as a categorical within-subject variable with four levels (T0 = baseline; T1 = pre-intervention; T2 = post-intervention; T3 = follow-up). Centre and tDCS condition (active vs. sham) will be included as between-subject variables. Given the staged recruitment, cohort will be included as a fixed-effect covariate to account for cohort-related differences over time (e.g., staff changes or evolving site practices). Models will include a random intercept for baseline differences across individuals, and, where supported, a random slope for timepoint will allow individual trajectories over time (simplified if convergence issues arise). Fixed effects will be estimated for timepoint, tDCS condition, centre, cohort, and their relevant interactions. We will set T1 (pre-intervention) as the reference level to be able to compare T0 vs. T1 (changes during waitlist period), T2 vs. T1 (changes during intervention), and T3 vs. T1 (longer-term changes).

The primary CR effect will be evaluated by comparing changes observed during the intervention period with changes during the waitlist period, pooling across tDCS conditions. The tDCS augmentation hypothesis will be tested via the intervention × timepoint interaction, operationalised as the difference in change from T1 to T2 and from T1 to T3 between active tDCS and sham tDCS. Given the trial is powered for the primary within-subject CR effect rather than the between-group tDCS contrast, tDCS results will be interpreted as secondary and hypothesis-generating, emphasising effect size estimates and 95% confidence intervals.

We have three primary outcomes (GAS, ILSS-O, ILSS-SR). To control multiplicity, we will control the family-wise Type I error rate across the three primary outcomes at two-sided α = 0.05 using the Holm correction.

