### Interventions

CR and tDCS are delivered individually, twice weekly for 16–20 weeks, equating to 32–40 sessions. Given that missed sessions may occur over this period, intervention completion is defined as attending at least 20 sessions, in line with the developers’ recommendations [44]. Each session lasts 30–45 min, depending on the participant’s attention span, with tDCS applied concomitantly during the first 20 min of CR. Therapists determine the total number of sessions required based on individual progress and needs. Missed sessions are not rescheduled. Before, throughout, and after the study, participants continue to receive treatment as usual, including therapies and activities such as cognitive behavioural therapy, creative therapy, or psychomotor therapy tailored to each individual’s needs.

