##### Daily living skills

 The Independent Living Skills Survey (ILSS) measures the basic functional living skills and has acceptable psychometric characteristics [79, 80]. Both the Self-Report (ILSS-SR) and the Informant (ILSS-I, completed by the participants’ case manager) versions are utilised. The ILSS-SR comprises 70 items, nine of which are interviewer-rated, scored as yes, no, or not applicable. The ILSS-I includes 102 items rated from 0 (never) to 4 (always). Total scores are summed and averaged per domain, with higher scores indicating better performance.

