This is among the first large-scale clinical trials to systematically evaluate CR combined with tDCS, moving beyond prior small pilot studies [65]. Several design features strengthen its scientific and practical value. First, the multi-centre approach increases the generalisability of the results. Second, regular supervision by an experienced clinical therapist will provide fidelity and consistency in intervention delivery. Last, the within-subject design allows participants to serve as their own controls through the waiting period. While the absence of a separate control group receiving only CR or an active control condition is a limitation, this design is particularly advantageous due to the heterogeneity of the target population, the higher feasibility because fewer participants are needed, and the focus on individualised goals.

Clinical trials in this population often face challenges such as recruitment and retention difficulties, particularly among individuals with low motivation or residing in less supportive environments. Insights from our pilot study enabled proactive strategies to anticipate and address these challenges. Despite concerns about recruitment, retention, or discomfort with tDCS posing barriers, particularly in a population with symptoms such as lack of trust or suspiciousness, the pilot demonstrated high acceptability and minimal attrition. In the present trial, active involvement of service users ensures alignment with the needs and experiences of the target population, which may improve both trial design and recruitment strategies. To illustrate, participants receive detailed information about tDCS and its potential side effects, and trainers monitor well-being throughout the sessions. If a participant refuses stimulation during a session, CR continues without tDCS, with reattempts in later sessions. Regular contact during the waiting period supports engagement, and offering home-based sessions when needed provides flexibility to maintain it further. Additional challenges include using research staff as trainers rather than professionals embedded within routine care. While this ensures consistent delivery of CR, it may limit direct transfer to clinical practice. To mitigate this, healthcare professionals are actively involved, and strategies are pursued to stimulate integrations of CR into standard practice.

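### The primary models have no trainer level, yet CR is given one-to-one by trainers and only after T1, so any trainer variance makes the standard error of the primary CR contrast too small

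*Protocol article*

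**What the plan says.** All places are in the protocol article.

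- **Statistical analysis.** The dependence structure is stated outright: "This approach accounts for the nested structure of repeated measures within participants and participants nested within centres". The terms follow: "Models will include a random intercept for baseline differences across individuals", a participant slope for timepoint where the data support it, and fixed effects for timepoint, tDCS condition, centre, cohort and relevant interactions. Cohort is included partly because staff may change. The primary CR effect is the change during intervention compared with the change during the waitlist, pooled over tDCS arms. Holm controls the family-wise error of the three primary outcomes at two-sided 5%.
- **Trial design.** Participants wait 16 weeks between T0 and T1. Randomisation and CR come after T1.
- **Interventions.** Sessions are individual, with 32-40 planned. "Therapists determine the total number of sessions required based on individual progress and needs".
- **Discussion.** On who delivers CR: "Additional challenges include using research staff as trainers rather than professionals embedded within routine care".
- **Proposed sample size and power calculation.** The basis is given as follows: "Using a paired t-test for dependent groups (two-sided α = 0.05, power = 0.80, Cohen’s d = 0.36), a sample size of 50 participants per group is required". Inflation for attrition then leads to the recruitment target: "To account for an estimated dropout rate of 20%, we aim to recruit a total of 126 participants, equating to 63 individuals per group". No allowance is made for clustering.

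**The concern.** The claim that the model handles the nesting is incomplete for the design described. CR is a guided therapy, and the Background lists guidance by a trained therapist among its core components. If some trainers get better results than others, participants who share a trainer have correlated changes.

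The timing matters. A stable participant, centre or cohort level cancels from (T2-T1)-(T1-T0). A trainer effect does not, because no one has a trainer at T0 or T1. Participant intercepts and slopes are independent between people, so they cannot carry correlation between people who share a trainer.

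The primary CR claim is the one exposed: its intervals would be too narrow, and Holm would be applied to p-values that are too small. The active-versus-sham comparison is largely protected if each trainer treats both arms, because the trainer effect then mostly cancels.

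**Working it through.** **The plan's own figures.** From the sample size section: two-sided 5%, power 80%, d = 0.36, paired t-test, 50 per group, 20% dropout. 50/0.8 = 62.5, rounded up to 63; 2 x 63 = 126; 126 x 0.8 = 100.8, so about 100 completers. The 50 itself is not reproduced. A two-sided paired t-test needs 63 pairs in total (normal approximation (1.960 + 0.842)^2/0.36^2 = 60.6, so 61), and 50 matches a one-sided test. That is a separate matter; only the 100 completers are used here.

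**How the trainer effect enters.** The contrast per participant is T2 - 2 x T1 + T0. With a trainer effect u at T2 only, u has coefficient 1. With K trainers and equal caseloads it adds var(u)/K to the variance of the estimated mean, and the planned model has no term for this.

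**Formulas.** Caseload m = 100/K. Design effect DE = 1 + (m - 1) x ICC, with the ICC on the contrast scale. Real two-sided error = 2 x (1 - Phi(1.96/sqrt(DE))). Assumed, because the article does not give them: K, the ICC, equal caseloads and one trainer per participant.

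**ICC of 0.05 on the T2 score.** With equal visit variances of 1 and visit correlation r, the contrast has variance 6(1 - r): 3.0 at r = 0.5 and 1.8 at r = 0.7. The contrast ICC is then 0.05/3.0 = 0.0167 or 0.05/1.8 = 0.0278.

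| Trainers | DE, r = 0.5 | Real error | DE, r = 0.7 | Real error |
|---|---|---|---|---|
| 5 | 1.32 | 8.8% | 1.53 | 11.3% |
| 8 | 1.19 | 7.3% | 1.32 | 8.8% |
| 12 | 1.12 | 6.4% | 1.20 | 7.4% |

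Simulation of a one-sample t-test on the contrast under these assumptions gave 6.4-11.0%. A t-test on trainer means stayed at about 4-5%.

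**ICC of 0.05 on the contrast itself.** For 8 trainers, DE = 1 + 11.5 x 0.05 = 1.575, and the error is 11.8%. It is 16.0% with 5 trainers, 9.4% with 12 and 7.4% with 20. With a contrast ICC of 0.02 the four figures (5, 8, 12, 20 trainers) are 9.5%, 7.7%, 6.7% and 5.9%.

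**Do centre and cohort absorb it?** As main effects they cancel from a change contrast. A simulation with 6 trainers and contrast ICC 0.05 gave 13.5% without adjustment and 15.0% with centre-by-time and cohort-by-time terms. At ICC zero both were close to 5% (5.0% and 5.6%).

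**Power.** Phi(0.36 x sqrt(100/DE) - 1.96) gives 94.9% at DE = 1. With 8 trainers it is 88-91% if the ICC of 0.05 is on the T2 score, and 82% if it is on the contrast. The last figure drops to 69% with a t reference on 7 degrees of freedom.

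**The case against.** **Trainer variance may be small.** CR is a computerised programme. The Cognitive remediation section requires official training and continuing supervision, and the Discussion says that using research staff keeps delivery consistent. Session numbers are tied to participant progress, so trainer discretion over dose does not itself show a trainer effect. All of this stands: it could bring the inflation near zero. It does not show that the variance is zero, and the planned model cannot reveal it.

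**The facts needed to size it are missing.** The article gives no trainer count or caseload and does not say whether a participant keeps one trainer; sharing trainers would dilute the clustering. A reader might infer a small fixed pool of trainers, or a standard error that is certainly wrong. The text supports neither. That each trainer treats several participants is a probable inference from research staff serving 126 people.

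**This could be left to an SAP.** Degrees of freedom and sensitivity analyses often are. But the article names the nesting levels and says the model accounts for them, so the structure is fixed here and lacks a level.

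**Three stronger readings do not hold.**
- Leading with 16%. An ICC of 0.05 on the contrast means about 0.15 (0.05 x 3.0) or 0.09 (0.05 x 1.8) on the T2 score, which is demanding.
- Sizing the problem on T2-T1 alone, where it would look larger. The Statistical analysis section defines the primary CR effect as a comparison of the two periods.
- Adding a case-manager effect for the informant ILSS. The article says only that it is "completed by the participants’ case manager". Nothing shows that one rater covers several residents or that ratings shift together, and a stable rating style cancels from change.

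**Conclusion.** The point holds in conditional form. The stated structure omits a level that acts only after T1 and so falls wholly into the primary contrast. For any trainer variance above zero the standard error is too small when the conclusion is meant to reach beyond these trainers, which the Discussion's aim of use in standard care implies.

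The size cannot be derived from the article. On the assumptions in the working, the real error of each nominal 5% test is about 6-11% with the ICC of 0.05 on the T2 score, about 9-16% with it on the contrast, and 5% with no trainer variance. The 100 expected completers exceed the 63 pairs that a two-sided paired test needs, which cushions power up to a design effect of about 100/63 = 1.6. That surplus does not correct the standard error or the type I error.

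**What to change.** - Record the treating trainer for every participant, including any change of trainer.
- In Statistical analysis, add a trainer random effect that acts only on post-T1 visits, for example (0 + post | trainer) with post = 1 at T2 and T3. Use Satterthwaite or Kenward-Roger degrees of freedom. Kenward-Roger rests on a REML fit, so choosing it means editing the maximum likelihood sentence too.
- If that component cannot be estimated, use CR2 cluster-robust standard errors by trainer with small-sample degrees of freedom.
- Base the three Holm-controlled tests on these standard errors.
- Amend the sentence on nesting to name the trainer level.
- State in the sample size section that the power assumes no trainer clustering.

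No case-manager random effect is needed on the present text.

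The cost is one identifier and some analysis wording, with no extra participants or visits. Recruitment is still open, with 59 enrolled at submission. The downside is wider intervals, fewer degrees of freedom if trainers are few, and a less favourable power statement.
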